## Abstract

**Background:**

laminectomy is a valuable surgical treatment for some patients with a cervical radiculomyelopathy due to cervical spinal stenosis. More recently attention has been given to motion of the spinal cord over spondylotic spurs as a cause of myelopathic changes. Immobilisation by fusion could have a positive effect on the recovery of myelopathic signs or changes. This has never been investigated in a prospective, randomised trial. Lamifuse is an acronyme for laminectomy and fusion.

**Methods/Design:**

Lamifuse is a multicentre, randomised controlled trial comparing laminectomy with and without fusion in patients with a symptomatic cervical canal stenosis. The study population will be enrolled from patients that are 60 years or older with myelopathic signs and/or symptoms due to a cervical canal stenosis. A kyphotis shape of the cervical spine is an exclusion criterium. Each treatment arm needs 30 patients.

**Discussion:**

This study will contribute to the discussion whether additional fusion after a cervical laminectomy results in a better clinical outcome.

**ISRCT number:**

ISRCTN72800446

## Background

Cervical spondylosis is a progressive degenerative disease of the spine. As people grow older, the prevalence of cervical spondylosis increases. It is a natural process of aging. Cervical spondylosis is seen in 10% of individuals in the age of 25 years, whereas in 95% of the persons of 65 years [1].

Due to the degenerative process reduction of height of the intervertebral discs, formation of spondylophytes and sometimes instability occurs. This may lead to a stenosis of the cervical spinal canal. In most instances it will remain asymptomatic. However, in some persons the stenosis of the spinal canal leads to a compression of the spinal cord. It is important to realize that not only static compression leads to neurological symptoms, but also dynamic factors do. In a normal situation the spinal cord will move during flexion and extension. Ventral osteophytes in the spinal canal prevent up – and downward movement [1]. Furthermore, the spinal cord is more stretched over the anterior bars increasing axial tension within the spinal cord. These forces are multidirectional creating secondary shearing forces resulting in stretch and shear injury to myelin and neural elements [2-4].

Patients may present with a diversity of well known signs and symptoms with variable intensities. Disturbance of the sensibility in the arms, clumsiness of the hands and problems with micturation may occur. However, the hallmark symptoms are gait abnormalities, weakness of the legs or stiffness of the legs [1,5].

The natural course of the cervical myelopathy is variable. But patients developing mild or moderate symptoms are less likely to improve spontaneously. Non operative treatment will mainly affect neck pain or accompanying radiculopathy. Improvement has been noted but is variable [6,7]. Patients with myelopathic signs and symptoms will, however, likely benefit from surgery [5,7,8].

Surgical approaches for cervical myelopathy due to cervical spondylosis can be anterior, posterior or combined. The last option is reserved for deformity correction. In most instances a lordotic or slight kyphotic cervical spine is present. The choice for an anterior or posterior approach is dependent on the main site of compression, the shape of the cervical sagittal curvature and to a lesser account on the preference of the surgeon.

Dorsal approaches are laminectomy or laminoplasty. A difference in clinical outcome has never been established. Prevention of post – laminectomy kyphosis is a reason for laminoplasty. If an additional, instrumented dorsal fusion is performed, the change of developing a post-surgical kyphosis is nearly zero[9]. It should be memorized that spondylotic processes also generate reduced motion of the spinal segments, a natural course [1]. From this point of view, decompression with fusion will have better clinical results when compared to decompression solely. In literature, indications in this direction are found. Frequently used dorsal fusion techniques today use lateral mass screws and cervical pedicle screws. This is relatively safe with a minimal persistent complication rate. Furthermore, in experienced hands these techniques do not add substantial time to the duration of the surgery [7,9].

Despite a long-lasting interest in the various techniques, the clinical superiority of one method over the other has never been established. To our knowledge, a randomized controlled trial comparing laminectomy with or without fusion has never been performed.

## Methods/Design

### Hypothesis

Patients that are surgically treated for signs and symptoms due to a stenosis of the cervical spinal canal have a better clinical outcome when a dorsal fusion is performed in addition to a laminectomy compared to those that have solely a laminectomy.

At the end of the study, the quality of life, complications, and the costs will be evaluated comparing these two treatment groups.

### In – and exclusion criteria

Patients with a minimal age of 60 years are included (Table 1). At neurologic examination myelopathic changes must be apparent. At magnetic resonance imaging, concordant stenotic alterations at the cervical level(s) must be present. At the plain sitting lateral radiograph a lordotic spine must be shown. The shape of the cervical spine is lordotic when the vertebral bodies of C3 to C6 are in front of a line drawn from a point of the posterior inferior part of the vertebral body of C2 to a point at the posterior superior part of the vertebral body of C7 (Figure 1).

**Figure 1 F1:**
[figure not shown]
Line from the posterior inferior part of the vertebral body of C2 to the posterior superior part o f the vertebral body of C7 in case of a normal cervical lordotic curvature (A) and a kyphotic cervical curve (B).

**Table 1 T1:** in – and exclusioncriteria

Inclusion	Exclusion
60 years or older	Previous cervical surgery for myelopathic signs and symptoms
Cervical myelopathic symptoms and or signs at neurologic examination	Solely radiculopathy, or most important complaint
Stenosis of cervical spinal canal at MRI	Unable to undergo MRI
Lordotic shape at lateral cervical plain radiograph, or at lateral cervical radiograph in extension	Life expectancy less than 2 years
Informed consent	Other diseases interfering with neurologic symptoms and signs, for example spinal cord glioma, thoracic herniated disc with spinal cord compression, multiple sclerosis etc.
	Rheumatoid arthritis
	Trauma to the neck in history
	Diseases interfering with rehabilitation, for example severe cardiac congestive disease.
	Participation in another study

Only patients that sign the informed consent after some time of reflection (1 week) are included.

### Clinical evaluation and follow up

At the first intake, duration of symptoms, other diseases, severity of signs and symptoms are noted. Neurologic examination is performed by an independent neurologist. At follow up, the severity of signs and symptoms are also noted. Special attention is given to the myelopathic changes in arms and/or legs. Furthermore, the clinical situation is evaluated by the modified Japanese Orthopaedic Association functional score[10] translated into the Dutch language. The validation of the Dutch translation is currently subject of investigation. Finally, a change in the quality of life is evaluated by the Dutch Short Form – 36 Health Survey.

Follow – up will be at six weeks, six months, and after one year postoperatively (Table 2). Complications are noted for their nature, duration and severity

**Table 2 T2:** overview of investigations at each clinical contact

	Preoperative	Postoperative (po)	6 weeks po	3 months po	1 year po
MRI	**X**				
Plain cervical radiograph	**X**	**X**	**X**	**X**	**X**
mJOA	**X**		**X**	**X**	**X**
SF-36	**X**		**X**	**X**	**X**
Neurologic examination by independent neurologist	**X**		**X**		**X**

### Surgical technique

Cervical laminectomy of the compressed levels is performed. Previous to the laminectomy a dorsal fusion is done. Dorsal fusion includes lateral mass screws from C2 to C6. In C2, C7 and the upper thoracic spine levels, pedicle screws will be placed. The screws are connected by rods or plates. Transverse connectors are used when indicated. In order to keep the posterior tension band intact, the fusion will extend from one level above the planned most cranial laminectomy level to at least one level below the most caudal planned laminectomy site. If the lowest level of fusion would include C7 or lower extension of the fusion to the upper thoracic spine (Th2 or Th3) is recommended[11]. This extension of the fusion is thought to prevent junction disease at the cervicothoracic junction. For example, if the laminectomy includes the levels C4 to C6, the fusion would be from C3 to C7. Because C7 is the lowest fusion level, incorporation of Th1 is recommended.

### Surgical demands

Since fusion is added, only centres with a known spinal surgical experience are asked to participate. The surgeons performing a laminectomy should also be experienced in lateral mass fixation techniques, especially lateral mass and cervical pedicle screws.

### Statistical analysis

The primary endpoint is clinical outcome after 1 year using the modified Japanese Orthopaedic Association functional score. Secondary outcomes are cost-effectiveness, quality of life measured by the SF-36, and complications. Statistical analysis is performed by a blinded investigator. For Statistical analysis the SAS system is used. Descriptive statistics are used to describe baseline characteristics. For comparison between groups student-t tests or chi – square tests are used. Statistical significance is reached when p < 0.05. Risk ratios (RR) and 95 % confidence limits (CI) are presented. All analyses are done according to the intention – to – treat principle

The minimal clinically important difference was estimated by asking 4 international active spine surgeons what they would consider a clinically significant difference in mJOA score. The mean of the values is considered the MCID.

The sample size is calculated as follows: a difference of at least two points on the modified JOA functional score is considered significant. The difference is expected to be mainly allocated to the function of the arms and legs. Based on literature, a standard deviation of approximately 2 is assumed [12]. A two group student t test with a 0.05 two sided significance level and a power of 95 % will need a sample size per group of 27 to detect a significant difference. Considering a ten percent of lost to follow up, a total of 30 individuals per group will be included.

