### Randomisation

For randomisation, the closed envelope method is used. As soon as informed consent is obtained, one of the treatment options is assigned to the patient. The secretary of the neurosurgical department in the Canisius Wilhelmina Hospital, Nijmegen, the Netherlands will control the randomisation. Prior to surgery, the patient is informed about the chosen option. Patients who do not choose for participation, are offered one of the surgical options that are currently under investigation. However, they are not followed in an observational cohort study.

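### The planned unadjusted t-test leaves the preoperative mJOA unused, an avoidable loss of precision in a trial of 30 per arm

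*Protocol article*

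**What the plan says.** The Statistical analysis section defines the endpoint: "The primary endpoint is clinical outcome after 1 year using the modified Japanese Orthopaedic Association functional score". The planned method is general and covers all outcomes: "For comparison between groups student-t tests", with chi-square tests as the alternative. Baseline characteristics are to be described only; no covariate is named.

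The sample-size paragraph ties the same test to the mJOA: "A two group student t test with a 0.05 two sided significance level and a power of 95" percent. Its inputs are a target ("a difference of at least two points on the modified JOA functional score is considered significant") and a spread ("a standard deviation of approximately 2 is assumed"). The result is that the trial "will need a sample size per group of 27 to detect a significant difference", raised to 30 per group for 10% loss to follow-up.

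Table 2 in Clinical evaluation and follow up, the "overview of investigations at each clinical contact", marks the mJOA preoperatively as well as at the postoperative visits. The Randomisation section describes closed envelopes and mentions no stratification by severity.

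**The concern.** The preoperative value of the primary outcome is usually the strongest predictor of its later value. Here it is scheduled for every patient but has no role in the comparison. The Background section describes symptoms of varying intensity, and Table 1 sets no mJOA range for entry, so baseline scores can be expected to vary.

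Two things are at stake. Variation in the 1-year score that the preoperative score could explain stays in the error term and widens the confidence interval. And with about 30 patients per arm and no stratification by severity, the arms may differ by chance before surgery; an unadjusted estimate carries part of that difference.

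The text also does not say outright whether the t-test is applied to the 1-year score or to the change from baseline, nor which of the two has the SD of 2.

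**Working it through.** **Inputs from the Statistical analysis section:** difference 2 points, SD 2, two-sided alpha 0.05, power 95%, 27 evaluable and 30 enrolled per arm. **Not in the documents:** the correlation r between preoperative and 1-year mJOA (assumed 0.3 to 0.7, with 0 as the worst case) and the SD of the preoperative score (assumed 2 in step 3).

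**1. The plan's own figure.** Exact noncentral-t power for a two-sample t-test with difference 2 and SD 2:
- 26 per arm: 94.2%
- 27 per arm: 95.0%

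Allowing for 10% loss, 27 / 0.9 = 30. Both stated sizes reproduce.

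**2. Precision with and without the baseline score, 27 per arm.**
Unadjusted: SE = 2 × sqrt(2/27) = 0.544. With 52 degrees of freedom the 95% CI half-width is 2.007 × 0.544 = 1.09 points.
ANCOVA: residual SD = 2 × sqrt(1 − r²), degrees of freedom 2 × 27 − 3 = 51. This ignores the small inflation of the SE from chance imbalance in the covariate.

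| r (assumed) | Residual SD | SE | 95% CI half-width | Power, 2 points | Power, 1 point |
|---|---|---|---|---|---|
| unadjusted | 2.00 | 0.544 | 1.09 | 95.0% | 44% |
| 0 | 2.00 | 0.544 | 1.09 | 95.0% | 44% |
| 0.3 | 1.91 | 0.519 | 1.04 | 96.5% | 47% |
| 0.5 | 1.73 | 0.471 | 0.95 | 98.6% | 55% |
| 0.7 | 1.43 | 0.389 | 0.78 | 99.9% | 71% |

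The variance of the estimate falls by about r²: 9%, 25% and 49%. At r = 0 the lost degree of freedom moves power from 95.01% to 94.99%.

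**3. Chance baseline imbalance, 30 per arm, baseline SD assumed to be 2.**
SE of the difference in mean preoperative mJOA = 2 × sqrt(2/30) = 0.516.
- P(difference beyond 0.5 points either way) = 2 × [1 − Φ(0.5/0.516)] = 33%
- P(difference beyond 1 point either way) = 2 × [1 − Φ(1/0.516)] = 5%

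With equal SDs at baseline and 1 year, an imbalance d shifts the expected unadjusted 1-year difference by r × d:
- d = 0.5: 0.15, 0.25 and 0.35 points at r = 0.3, 0.5 and 0.7
- d = 1: 0.3, 0.5 and 0.7 points

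**4. If the change score were t-tested instead.** If 2 is the SD of the score at each time point, the SD of change is 2 × sqrt(2(1 − r)). With 27 per arm and a difference of 2:

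| r (assumed) | SD of change | Power |
|---|---|---|
| 0.3 | 2.37 | 86% |
| 0.4 | 2.19 | 91% |
| 0.5 | 2.00 | 95% |
| 0.7 | 1.55 | 99.6% |

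Power falls below the stated 95% only when r is under 0.5. At every r shown in both tables the change-score analysis has less power than ANCOVA.

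**The case against.** The best defence is that nothing here is wrong. The sample size assumes a two-group t-test and the analysis uses one, so the two agree. Under randomisation the unadjusted test is unbiased, and its type I error and confidence interval already allow for chance imbalance. Covariates are often left to an analysis plan, which is not shown. Against the stated target the power gain is small, and the larger gains rest on a correlation the documents do not supply.

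Most of this stands and limits the weight of the point. It does not remove it: the article states the test and ties it to the mJOA in the sample-size paragraph, so the unadjusted comparison is a stated choice and not a gap awaiting detail.

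A reader might infer three stronger things that the documents do not support:
- **That an imbalance enters the 1-year result in full.** Only about r times the imbalance does (step 3).
- **That the trial is underpowered because change may be the outcome.** The endpoint wording and the Primary endpoints section, which places evaluation at one year, most naturally mean the 1-year score. Even for change, power reaches 95% at r = 0.5 and exceeds it above that.
- **That the preoperative mJOA may be taken after allocation is known.** The Randomisation section says "As soon as informed consent is obtained, one of the treatment options is assigned to the patient", but severity is noted at first intake, and the inclusion criteria section requires a week of reflection before consent. No passage places the baseline score after the envelope is opened.

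**Conclusion.** The point holds as a recommendation on efficiency and robustness. It is not a finding of bias or of a wrong sample size: 27 and 30 per arm at 95% power are correct for the stated inputs.

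The gain depends on r. It is modest at 0.3 (half-width down by 0.05 points) and substantial at 0.7 (down by 0.31 points, from 1.09 to 0.78). It matters most if the true effect is smaller than planned: for a 1-point difference, power would be 47% to 71% over the assumed range, against 44% unadjusted. The imbalance figures rest further on a baseline SD of 2, which the documents do not state. That no adjustment is planned is certain from the text; the size of the benefit is not. Because the downside at r = 0 is negligible, the change is worth making even without knowing r.

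**What to change.** In the Statistical analysis section, state the primary analysis as ANCOVA of the 1-year total mJOA on treatment group, with preoperative total mJOA as covariate. Report the adjusted mean difference with its 95% CI, and keep the unadjusted t-test as a supportive analysis. This also settles score versus change, because with the preoperative score as covariate both give the same treatment estimate.

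The cost is a sentence or two of wording, settled before unblinding so that the choice cannot depend on the results. It needs no new data or extra patients, and the sample size need not change.

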#### Secondary endpoints

Since instrumentation is added in the fusion group, the costs will be higher. On the other hand, it is assumed that a mean better recovery will take place in the fusion group. Therefore, the additional costs (nursing costs, auxillary supports, etc.) may be lower. A careful evaluation of the costs of the treatment related to the outcome is performed. To obtain a reliable insight in the costs the following will be noted in a kind of diary: hospitalisation, out – patient contacts, additional medication, house keeping support, instruments to support daily activities, e.g. walking, eating etcetera. Of each item the sort and amount will be recorded.

Apart from the cost – effectiveness, the difference in the general health status will be evaluated. It is assumed that general health will improve more after of a laminectomy with a fusion than one without. This will be reflected in a difference of the SF – 36 score. The Short Form 36 Health Status Questionnaire is a widely-used generic health status. This instrument consists of eight subscales and two summary scales. On each scale higher scores indicate better outcomes. Scores can be compared with published age – and sex – matched general population or disease-specific norms [14]. Furthermore, it has been validated for cervical spondylotic myelopathy [15].

Complications are separately registered. Complications related to the cervical myelopathy are postoperative hemorrhage, postoperative infection, temporary or permanent impairment of neurologic function, and kyphotic deformation of the cervical spine[7]. Complications related to adding lateral mass screws or/and pedicle screws are vertebral artery injury and temporary or permanent nerve root damage[7]. In order to prevent damage to the spinal cord, the instrumentation should be completed before the laminectomy.

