### Monitored events

Monitored events are the death of a patient, withdrawal from the study, lost to follow – up, and cross – over from their randomly assigned treatment group. These events are registered within the case record form. The circumstances of the events are investigated and also noted. In case of death of the patient, a search for a relationship with the instituted treatment is started. Throughout the study, all medical complications and intervening treatments concerning the cervical spine are registered within the CRF at the usual follow – up visits or when the appropriate information reaches the treating surgeon.

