### Protocol violations

Any of the following will be considered as a deviation from the protocol: randomization of an ineligible patient, enrollment of a patient that is already participating in an another study, enrollment of an participant to this study in another study, a patient receiving the wrong treatment, loss of radiology or any other data, and informed consent violations. Violations are reviewed monthly and reported to the independent study supervisor ([name], M.D., Canisius Wilhelmina Hospital, Nijmegen).

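### Intention-to-treat is fixed as the only analysis of complications, although cross-over is provided for and some complications are tied to the screws; a second table by procedure attempted should be added

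*Protocol article*

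**What the plan says.** Protocol article, Statistical analysis: "Secondary outcomes are cost-effectiveness, quality of life measured by the SF-36, and complications". The same paragraph provides for chi-square tests between groups, says that "Risk ratios (RR) and 95 % confidence limits (CI) are presented", and closes with the rule "All analyses are done according to the intention"-to-treat principle. No exception is made for complications, and the article describes no table by operation received.

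Three other places bear on this rule:

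- Monitored events provides for patients crossing "over from their randomly assigned treatment group", without a rate or direction.
- Protocol violations lists "a patient receiving the wrong treatment".
- Secondary endpoints says: "Complications related to adding lateral mass screws or/and pedicle screws are vertebral artery injury and temporary or permanent nerve root damage". A separate list covers complications related to the myelopathy itself.

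The Hypothesis section adds that complications will be compared between the two treatment groups, so more than a listing is intended.

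**The concern.** The article separates screw-related harm in its definitions but prescribes a comparison that ignores whether screws were placed. Under that rule, a vertebral artery injury in a patient allocated to laminectomy but actually fused counts in the laminectomy arm. A patient allocated to fusion who never received screws stays in the fusion denominator. Both pull the arms together, so the added risk of instrumentation looks smaller than it is.

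Cross-over is practicable here. Patients learn their allocation before surgery (Randomisation), and the surgeons who perform laminectomy should also be experienced in the fixation techniques (Surgical demands). At stake is a fair description of what the instrumentation adds in risk, in a trial of 60 patients with few such events to count.

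**Working it through.** **Arm size.** The plan states "0.05 two sided significance level and a power of 95 % will need a sample size per group of 27", for a difference of 2 points and a standard deviation of 2. The normal approximation gives 2 × (1.960 + 1.645)² × 2² / 2² = 25.99, so 26. The exact t-test calculation gives 26.99, so 27, with power 0.950. Allowing for 10% loss, 27 / 0.90 = 30 per group. The stated figures reproduce and are not in dispute; 30 per arm is used below.

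**Inputs not in the protocol, taken as assumptions.**

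- c1: proportion of the laminectomy arm that is fused.
- c2: proportion of the fusion arm that is not fused.
- b: background risk of the complication without screws.
- h: excess risk when screws are placed.
- Cross-over is unrelated to a patient's complication risk.

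**Risk by allocation.**

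- Laminectomy arm: b + c1 × h
- Fusion arm: b + (1 - c2) × h
- Difference: h × (1 - c1 - c2)

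The true difference is h, so the by-allocation analysis shows the fraction 1 - c1 - c2 of it, whatever b and h are.

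| c1 | c2 | fraction of true excess shown |
|---|---|---|
| 0 | 0 | 100% |
| 5% | 0 | 95% |
| 10% | 0 | 90% |
| 5% | 5% | 90% |
| 10% | 10% | 80% |
| 15% | 15% | 70% |

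**Risk ratio, the planned effect measure.** With b = 5% and h = 10%, the true ratio is 0.15 / 0.05 = 3.00.

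- c1 = 5%, c2 = 0: 0.150 / 0.055 = 2.73
- c1 = 10%, c2 = 0: 0.150 / 0.060 = 2.50
- c1 = c2 = 10%: 0.140 / 0.060 = 2.33

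**Events expected in the wrong column.** Take h = 10% and count only screw-related events in the 30 patients allocated to laminectomy. The risk per patient from this source is c1 × h.

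| c1 | expected events, 30 × c1 × h | chance of at least one | chance of two or more |
|---|---|---|---|
| 5% | 0.15 | 1 - 0.995^30 = 14% | about 1% |
| 10% | 0.30 | 1 - 0.990^30 = 26% | about 4% |
| 15% | 0.45 | 1 - 0.985^30 = 36% | about 7% |

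One such event adds 1/30 = 3.3 percentage points to the laminectomy arm.

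**The case against.** The strongest reply is that comparing complications by allocation is not an error. It is protected by randomisation and answers a legitimate question: what happens under a policy of offering one operation or the other. That stands, and a reader who infers that intention-to-treat is wrong for complications goes further than the text allows.

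A second reply is that safety tables belong to an analysis plan that is not shown, and that the needed data are recorded anyway: complications are registered separately and by type, and cross-overs are noted with their circumstances. The point about the data stands and makes the fix cheap. The first half is weaker. The article does not leave the matter open; it sets one rule for all analyses, and recording events does not change the prescribed comparison.

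Third, the size of the problem is easily overstated. Cross-over is listed as something to monitor, not predicted. The article calls the listed injuries related to the screws; it does not say that only screws can cause them, so a zero risk without screws is not its claim. One might also infer that the safety conclusion would turn on several misplaced events. Under the assumptions above, two or more are unlikely (about 1% to 7%). Even without cross-over, 3/30 against 0/30 gives a chi-square p of about 0.08, so small numbers limit the safety comparison more than dilution does.

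Fourth, making a table by operation received the main safety analysis could mislead in the same direction. Screws go in before the laminectomy (Surgical technique, Secondary endpoints). If a screw injury led to the fusion being abandoned, the patient would have received laminectomy alone, and that table would charge the injury to laminectomy. This stands and shapes the fix.

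**Conclusion.** The point holds as a modest improvement to a stated rule. With intention-to-treat as the only analysis of complications, any cross-over reduces the apparent excess risk of screw-related harm to (1 - c1 - c2) of its true value, in favour of fusion: 90% at 5% each way, 80% at 10% each way. This rests on assumed cross-over rates and on cross-over being unrelated to complication risk. With no cross-over, there is no dilution.

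The documents do not support the stronger conclusions that the by-allocation comparison is invalid, that it should be replaced, or that it would by itself reverse the safety finding. The primary mJOA analysis and the sample size are untouched.

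**What to change.** Reword the closing sentence of the first paragraph of Statistical analysis. Intention-to-treat stays the rule for mJOA, SF-36, costs and the randomised comparison of complications. Add that complications are also tabulated by procedure attempted: any patient in whom screw placement was started counts as exposed to instrumentation, even if the fusion was abandoned, and all others count as laminectomy alone. List cross-overs by arm and direction beside the two tables.

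The cost is one sentence and one table. The protocol already provides for recording complications and cross-overs; the one thing to confirm is that the case record form shows whether screw placement was started. The downside is that the second table is not protected by randomisation, because patients who cross over may differ in risk. It should therefore stand beside the by-allocation table and never replace it.

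### The unadjusted t-test named for the 1-year mJOA is an inefficient way to deliver the claimed intention-to-treat comparison, and is open to bias if loss is informative

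*Protocol article*

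**What the plan says.** In the Protocol article, Statistical analysis, the primary endpoint is the mJOA at 1 year. Student t-tests or chi-square tests are named for comparing the groups. The sample size rests on the same test: "A two group student t test with a 0.05 two sided significance level and a power of 95" percent, giving 27 per group. The section then allows for attrition: "Considering a ten percent of lost to follow up, a total of 30 individuals per group will be included". It also says "All analyses are done according to the intention"-to-treat principle.

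Table 2 schedules the mJOA before surgery, at 6 weeks, at a middle visit and at 1 year. The middle visit is at 3 months in the table, but the text of Clinical evaluation and follow up gives "six months, and after one year postoperatively". All follow-up times are counted from surgery.

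Under Randomisation, treatment is assigned at consent, and "Prior to surgery, the patient is informed about the chosen option". Under Monitored events, departures from the study are recorded and looked into: "Monitored events are the death of a patient, withdrawal from the study", followed by loss to follow-up and cross-over. Nothing there says that such patients leave the analysis.

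**The concern.** Intention-to-treat settles which arm a patient is counted in. It does not supply a score that was never measured. A two-sample t-test on the 1-year mJOA therefore estimates the difference among patients who reach that visit, unless something is done about the others.

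That would matter little if loss were unrelated to outcome. Here patients know their arm before surgery, and the blinding described under Statistical analysis is that of the analyst. Loss after a poor recovery, a complication or disappointment with the assigned arm could differ between arms.

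The trial also collects three mJOA scores before the 1-year visit, and the named test ignores them. Those scores could improve precision and carry information about patients who are lost later. The Primary endpoints section itself cites a plateau in outcome at six months. If the middle visit is at six months, the plan's own premise makes that score highly informative about the 1-year score.

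**Working it through.** **Inputs.** All from Statistical analysis: difference 2 points, SD about 2, two-sided alpha 0.05, power 95%, loss 10%, 30 per arm.

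**1. The plan's own figure.** Two-sample t-test with the noncentral t distribution, df = 2n − 2, noncentrality = (2/2) × √(n/2):
- n = 26 per arm: power 0.9424
- n = 27 per arm: power 0.9501

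So 27 is the smallest number reaching 95%. Inflation: 27/0.9 = 30. Both figures reproduce.

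**2. What the inflation implies.** 30 × 0.9 = 27 patients per arm are expected to supply a 1-year score, and the stated power rests on them. If all 30 per arm had a score, the same test would have power 0.968. The 27 is thus the number the power calculation relies on; it is not a declared analysis set.

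**3. Data scheduled against data used.** Table 2 gives four mJOA assessments per patient; the t-test uses one. For complete data, the per-arm variance in the t-test is SD², whereas adjusting for baseline brings it to about SD² × (1 − ρ²), where ρ is the correlation of baseline with the 1-year score. The article gives no ρ, so the gain in precision cannot be put in figures here.

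**4. Size of a possible bias.** The deficits and the imbalance below are assumptions, not figures from the article. Let m be the number lost out of 30 in an arm and k the number of points by which lost patients score below that arm's completers. The completer mean then exceeds the all-randomised mean by (m/30) × k, and the bias in the difference is

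(m₁/30) × k₁ − (m₂/30) × k₂.

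| Lost, arm 1 | Lost, arm 2 | Deficit k | Bias (points) | Share of 2-point target |
|---|---|---|---|---|
| 3 | 0 | 2 | 3/30 × 2 = 0.2 | 10% |
| 3 | 0 | 4 | 3/30 × 4 = 0.4 | 20% |
| 6 | 0 | 2 | 6/30 × 2 = 0.4 | 20% |
| 6 | 0 | 4 | 6/30 × 4 = 0.8 | 40% |
| 3 | 3 | same in both arms | 0 | 0% |

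The rows with 6 lost are twice the planned rate in that arm. If the loss is in the fusion arm, the completer comparison flatters fusion; if it is in the laminectomy-only arm, it works against fusion.

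For scale, with SD 2 and 27 against 30 patients, the standard error is √(4/27 + 4/30) = 0.53. The bias with 3 lost is then 0.2/0.53 = 0.38 to 0.4/0.53 = 0.75 standard errors.

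**5. The clock.** Assignment happens at consent, and every follow-up time runs from surgery. A randomised patient who is never operated on therefore has no defined 1-year date. The article gives no expected number of such patients, so no size is attached to this.

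**The case against.** A reader might infer that the plan runs a completer analysis on 27 per arm under an intention-to-treat label, and that lost or unoperated patients drop out of the primary result. The article does not support that. The sentence about 30 per group is a routine and correct allowance for attrition, and it defines no analysis population. No section excludes anyone, and patients who cross over can be analysed as randomised. The postoperative clock leaves the date undefined for an unoperated patient, but does not remove that patient.

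Three further objections stand in part:
- **Missing-data rule.** This may sit in a full protocol or analysis plan that is not shown, so its absence from a journal article is not an error. That limits the point to the test that the article does name.
- **Assumed bias.** The bias figures depend on one-sided loss and chosen deficits. A 4-point deficit is twice the assumed SD, and equal loss with equal deficits gives no bias.
- **Limits of the remedy.** A repeated-measures model assumes missing at random, whereas the worry is outcome-related loss. It adds no postoperative information for a patient lost before any follow-up visit. It would therefore be too much to say that the early scores largely correct the bias.

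What remains is that the article fixes a method, and a better one is available from data it already schedules.

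**Conclusion.** The point holds as a criticism of the named primary test. The sample-size arithmetic is sound and the intention-to-treat commitment is not contradicted. But an unadjusted t-test on the 1-year score, without imputation, draws on an expected 27 of 30 patients per arm and leaves the other scheduled mJOA scores unused. It is less efficient than it need be, and open to bias in a trial where patients know their allocation.

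With loss at the planned rate but confined to one arm, and lost patients 2 to 4 points worse, the shift is 0.2 to 0.4 points. That would not by itself overturn a true 2-point difference, but it could matter to a smaller or borderline result. With balanced loss and equal deficits the shift is zero. These sizes rest wholly on assumption. The change is worth making because it is cheap, not because bias has been shown.

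**What to change.** 1. **Primary analysis.** Replace the t-test for the primary endpoint with a mixed model for repeated measures in all randomised patients as allocated. Use post-baseline mJOA at every scheduled visit, treatment-by-visit terms and an unstructured covariance, with baseline mJOA either constrained equal across arms or entered as a covariate. The 1-year treatment contrast is the primary estimate. The constrained form keeps patients who have only a baseline score in the model; the covariate form does not.
2. **Sensitivity analysis.** Vary the assumed deficit of lost patients separately by arm, for example from 1 to 4 points worse, and report how the 1-year contrast moves.
3. **Before fitting the model.** Reconcile the middle visit, which is six months in the text and 3 months in Table 2. Define the 1-year assessment date for any randomised patient who is not operated on, and seek the mJOA at that date.

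**Cost.** Analysis wording, a few lines in SAS (which the plan already uses), and follow-up of any patients not operated on. The sample size stays at 30 per arm. The downside is reliance on missing at random, which the by-arm sensitivity analysis is there to test. Patients lost before any follow-up visit still contribute no postoperative information.
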